**Figure 1 F1:**
[figure not shown]
Study outline.

### Plans for data storage, handling, and statistical analysis

2.4

Data storage and handling is under the supervision of a collaborator (biostatistician) from the Department of Biostatistics at NIMHANS. The data is coded and stored under password protection. Data analysis will also be carried out under the supervision of the Principal Investigator and the biostatistician. The person carrying out the analysis will be blind to subjects’ group allocation status. Intention to treat analysis and per protocol analysis would be done to account for the missing data. Interim analysis is planned at the end of 3 years of the study. There is no formal Data Monitoring Committee for the trial. However, a Trial Steering Committee is in place to monitor the conduct of the study. In addition, the Wellcome Trust - DBT India Alliance Expert Review committee reviews the trial annually and suggests modifications if needed. The NIMHANS Human Ethics Committee monitors ethical issues related to the trial.

Primary outcome measures: change in SAPS, SANS, BPRS scores and sub-scores; change in TRENDS accuracy scores (TRACS); change in serum BDNF; change in plasma oxytocin; and differences in BOLD response among study groups, and treatment effects (i.e., baseline vs follow-up comparison).

Secondary outcome measures: change in WHOQUOL-BREF scores; change in Perceived Stress Scale (PSS) scores; change in SOFS scores; change in serum cortisol; change in serum IGF-1; and change in gene expression of BDNF and oxytocin genes.

Physical activity levels of all subjects is obtained using a standard questionnaire and controlled for during analysis. Antipsychotic medication dosage would be recorded and analyzed as a covariate.

Data analysis will be done using SPSS Version 24 (IBM SPSS Statistics for Windows, Version 24.0. Armonk, NY: IBM Corp). Basic details of patients who opt out of the study are recorded, and measures to deal with dropouts, missing data, and non-adherence will be taken in collaboration with the biostatistician. Intent-to-Treat analysis will be done including data of all randomized subjects. Mixed model multivariate analysis will be used. Details of imaging analysis are given in the section on imaging below.

### Interventions

2.5

For yoga group—Validated Yoga Module for Schizophrenia—duration approximately 60 minutes.^[15]^

Treatment-as-usual (waitlist) group: This group will not receive any additional interventions. They are asked to continue with the prescribed medications, and requested to be available for assessments.

Previous studies in this area have noted changes after 1 month of yoga training and at 3 to 4 months follow up.^[18]^ However, there is no literature on the sustainability of the changes beyond 4 months and reviews on the subject have called for confirmation of the findings and longer follow-up. In this light, the proposed study aims to replicate the findings of the previous studies and extend the follow-up to 6 months. Other than the clinical rating scales, the other assessments are not expected to have significant issue with repeated measurements. Some of the measures which are not expected to change within a short period (SOFS, WHOQUOL-BREF) are to be repeated at baseline, 3 and 6 months only.

#### Description of some relevant assessments

2.5.1

(1)Tool for Recognition of Emotions in Neuropsychiatric disorders^[25]^ (TRENDS): This is a tool validated for use in the Indian population, which captures the full range and nature of emotional expressions akin to real life situations and can be utilized for behavioral and functional imaging studies in Indian patients. It takes into account variations of age and sex on emotional expressions and is a culture-sensitive tool. This is a culturally sensitive, ecologically valid tool, consisting of 52 static (still) and 28 dynamic (video clip) images (i.e., totally 80 images) of 6 basic emotions—happy, sad, fear, anger, surprise, disgust, and a neutral expression emoted by 4 experienced actors (1 young man, 1 young woman, 1 older man, and 1 older woman).(2)Socio Occupational Functioning Scale^[26]^ (SOFS): This is a comprehensive, easy to administer measure of social functioning in schizophrenia patients developed in India. The scale has 14 items rated on a 5-point spectrum (1 = no impairment, 5 = extreme impairment). The scale has a 3 factor structure comprising of adaptive living skills, social appropriateness, and interpersonal skills.(3)Perceived Stress Scale^[28]^ (PSS): The Perceived Stress Scale (PSS) designed by Sheldon Cohen is one of the most widely used psychological instruments for measuring the perception of stress. It is a measure of the degree to which situations in one's life are appraised as stressful. Items are designed to tap how unpredictable, uncontrollable, and overloaded respondents find their lives. The scale also includes a number of direct queries about current levels of experienced stress. The items are easy to understand, and the response alternatives are simple to grasp. Moreover, the questions are of a general nature and hence are relatively free of content specific to any subpopulation group. The questions in the PSS ask about feelings and thoughts during the last month. In each case, respondents are asked how often they felt a certain way.(4)Serum Cortisol, IGF-1, and BDNF estimation: Venous blood (around 5 mL) is collected from patients in anticoagulant-free tubes around 9 am and serum is separated after 30 minutes by centrifugation (2900 rpm for 15 minutes). Coded serum sample is stored at –80 °C deep freezer. Serum Cortisol, IGF-1, and BDNF levels are measured using Enzyme-linked Immuno Sorbent Assay (ELISA) by commercial reagents according to the manufacturer's instructions.(5)Plasma Oxytocin estimation: Blood sample is collected around 9 am after overnight fasting. Five cubic centimeter of blood is drawn and collected into chilled EDTA (1 mL/mL of blood) tubes containing aprotinin (500 KIU/mL). Sample is centrifuged at 1600 × *g* for 15 minutes at 2 to 8 °C. Plasma sample is immediately frozen and kept at –80 °C deep freezer till analysis. Plasma oxytocin levels will be measured by ELISA using commercial kits.

Note: All aseptic precautions will be taken while collecting blood to ensure patient safety.

(1)Gene expression studies:Lymphocytes Preparation: Peripheral blood (5 mL) is drawn from the cubital vein into using BD vacutainer. EDTA-treated blood is layered on the Ficoll Paque solution and centrifuged for a short period of time. The lymphocytes are then recovered from the interface between the plasma and the Ficoll-Paque and subjected to short washing steps with a balanced salt solution to remove any platelets, Ficoll-Paque and plasma. The resulting lymphocyte pellet is subjected to RNA preparation procedures. The choice of lymphocytes for gene expression studies is based on support for the usage of lymphocytes as a neural probe with promising utility for studying psychiatric disorders.^[33]^ Moreover, studies have demonstrated that altered T lymphocyte function in schizophrenia as a cellular model to investigate molecular disease mechanisms of this disorder.^[34]^RNA Isolation and Analysis: Total RNA is isolated from lymphocytes using commercial silica membrane based spin column method. In this procedure, the leukocytes are lysed using highly denaturing conditions that immediately inactivate RNases, allowing the isolation of intact RNA. RNA will get bound to the silica membrane during centrifugation, which is then washed and eluted in RNase-free water. RNA concentration is measured photometrically and purity checked through the ratio of optical density at 260 and 280 nm. The quality of the isolated RNA is checked by agarose gel electrophoresis (1% agarose, formaldehyde containing) through interpretation of 18 S and 28 S bands. Only high quality RNA is used for further analysis.cDNA-synthesis and Gene Expression Analysis: Total RNA is reverse-transcribed into first-strand cDNA by using commercial reverse transcriptase with RNase H activity and random hexamer/oligo-dT primers. A ribonuclease activity of RNase H of Reverse Transcriptase specifically degrades only the RNA in RNA: DNA hybrids. cDNA product is used as template for Quantitative real-time Polymerase Chain Reaction. Oxytocin and BDNF gene expression is analyzed quantitatively using TaqMan Gene expression assays with Real-Time PCR system (Applied Biosystems, CA, USA). The assay is validated using relevant endogenous control like GAPDH or β-actin used to normalize for differences in sample RNA added to a reaction.(2)Magnetic resonance imaging methods

MRI Scanner and related hardware: MRI data is acquired using 3T scanner (Ingenia CX, Philips Healthcare, Best, Netherlands, R5.3.1.2). For task-based functional MRI (fMRI), the following hardware are used: MR compatible display monitor (LCD, 32-in.), SyncBox (Nordic Neuro Lab Inc., Norway) and button response device (Current Designs Inc., PA).

##### MRI scanning: screening and training pre-scan assessments and training

2.5.1.1

MRI is done on the same day of the clinical assessment and blood sample collection. Patients are provided with the required information about the scanning procedures. They are trained by the clinician-researcher to familiarize themselves with the task-based fMRI experiments. The patients are comprehensively screened for MR safety by the clinical team, followed by on-site screening by the MRI center staff before the initiation of the scan. A fiducial marker (Capsule Vitamin E) is positioned at the right temporal region of the patients for ascertaining laterality of the MRI data. The following MRI scans are acquired:

Structural MRI (T1): T1-weighted single-shot 3D turbo field echo (TFE) image is acquired. Other parameters of the structural MRI scan are: TR = 2500 ms, TE = 2.9 ms, Flip angle = 9°, FOV = 256 mm covering the whole brain including cerebellum and brain stem, slice thickness = 1 mm without interslice gap, Matrix = 256 × 256; Voxel size = 1  mm × 1 mm × 1 mm, acceleration factor (SENSE) = 2, 192-sagittal slices.

Functional MRI (fMRI): The functional MRI scans (blood oxygenation level-dependent [BOLD] sensitive echo planar imaging [EPI] sequence) comprise of resting-state fMRI and task-based fMRI for emotion processing (emotions–matching and labeling task [E-MALT]). A second-order pencil beam shimming covering the entire brain is applied to facilitate homogenization of signal acquisition to minimize signal loss in certain susceptible regions like orbitofrontal cortex. Field map and phase-encoding EPI reference scans (with opposing polarity) are acquired along with other functional MRI scans (i.e., resting/E-MALT) for correction of geometrical distortion (if any) during image processing.

Resting-state fMRI (RS-fMRI): RS-fMRI is acquired in the eyes closed condition, and the participants would be instructed to relax, not think anything actively, and lay still. The scan is acquired with following parameters: TR = 2200 ms; TE = 28 ms; flip angle = 80°; slice-thickness = 3 mm; slice-order: ascending; slice-number = 44; Gap = 0.3 mm; Matrix = 64 × 64 × 64 mm^3^, FOV = 211 × 211, voxel = 3.0 mm isotropic with 275 dynamic scans.

##### Task fMRI-1: EMALT paradigm

2.5.1.2

The experimental paradigm consists of human faces depicting fear, anger, sad, and disgust emotions obtained from a validated tool culturally appropriate for Indian subjects—Tool for Recognition of Emotions in Neuropsychiatric Disorders (TRENDS).^[25]^ To explore the complex emotion processing function the TRENDS experiment was modified to incorporate emotion matching and labeling tasks based on pre-existing studies.^[35]^ In this experiment subjects perform 3 tasks; matching of facial emotions, labeling of facial emotions and a control task. In the matching task subjects are presented with a target face along with 2 other faces on the same screen. They are asked to select which one of 2 faces presented on the same screen expressed the same emotion as that of target face by pressing the buttons of the button response box. In the labeling condition, subjects view the same target face but have to judge which of two linguistic labels, given below the target best describes the target facial emotion. For each affect condition, 32 different images are used, 8 per block, 4 of each sex, and 4 of old age and 4 of young. Each block consists of images of either fear and anger/sadness and disgust of low and high intensity in separate blocks. For control task, 6 different geometric forms are used.

The paradigm consists of a total of 16 experimental blocks, 4 blocks each of matching and labeling emotions interleaved with 8 control blocks. Each matching and labeling block consist of 8 stimuli of 3500 ms duration and control block consisted of 4 stimuli of the same duration. Total block duration of matching and labeling task is 28 seconds and that of control block is 14 seconds. Total scan duration is 7:10 min. The blocks are presented in a pseudo randomized manner. Two paradigms are developed with a change in the order of the appearance of blocks. The appearance of stimuli within blocks is randomized. The paradigm is counterbalanced across subjects with respect to the type of emotions, the intensity of emotions and the sex and the age of the images. The paradigm begins with a control block followed by either matching or labeling task. The EPI sequence parameters are: TR = 2000ms; TE = 28 ms; flip angle = 80; slice thickness = 3 mm; Slice order: ascending; slice-number = 42; Gap = 0.3 mm; Matrix = 64 × 64 × 64 mm^3^, FOV=217 × 217 × 142 mm, voxel = 3.0 mm isotropic with 208 dynamic scans.

##### Task fMRI-2: tool for recognition of emotions in neuropsychiatric disorder (TRENDS) paradigm

2.5.1.3

The experimental paradigm consists of human faces depicting fear, anger, sad, disgust, and neutral emotions adapted from our previous publication.^[25]^ The faces are projected on a screen and subjects are instructed to passively view the images. The emotions are projected sequentially in a block design in the following order, Neutral, Sad, Disgust, Fear, and Anger. Each block consists of 8 stimuli consisting of an equal number of old and young men and women faces (high resolution 1920 × 1080 images). The first 4 stimuli are of mild intensity emotions and the next 4 stimuli are of higher intensity emotions. Each stimulus is displayed for 3500 ms duration interspersed with 500 ms of crosshair between each stimulus. The duration of each block is 32 seconds and these 5 blocks are repeated twice amounting to a total of 80 stimuli displayed over 5.3 minutes (320 seconds). The scan acquisition parameters are: TR = 2000 ms; TE = 28 ms; flip angle = 80; slice thickness = 3 mm; slice order: ascending; slice-number = 42; Gap = 0.3 mm; Matrix = 64 × 64 × 64 mm^3^, FOV = 217 × ∗217 × 142 mm, voxel = 3.0 mm isotropic with 160 dynamic scans.

##### Diffusion tensor imaging

2.5.1.4

DTI data is acquired to analyze the white matter metrics. To correct for potential geometric distortions during image processing, reference images (*b* = 0) are acquired in opposite phase-encoding directions (posterior-to-anterior and anterior-to-posterior). To minimize signal loss in susceptible regions, shimming is applied (similar to fMRI protocol). DTI is acquired with a-shell sampling protocol as described earlier.^[36]^ This DTI protocol ensures optimal angular coverage with resultant better angular resolution. The DTI parameters are: TR = 7226 ms, TE = 100ms, FOV = 240 × 240 × 140 mm, Voxel-size = 2.5 mm × 2.5 mm × 2.5 mm, Slice-thickness = 2.5 mm, no inter-slice gap, number of slices = 56, B0 = 7, B1000 = 25, B2000 = 24, B3000 = 24. In addition to this, a low *b*-value shell 500 smm^−2^ with 6 gradient directions are also acquired.

The fMRI processing and analyses will be carried out for all subjects using Statistical Parametric Mapping (SPM) software utilizing standardized processing steps (http://www.fil.ion.ucl.ac.uk/spm/). SPM combines the General Linear Model and Gaussian field theory to draw statistical inferences from blood oxygenation level-dependent (BOLD) response data regarding deviations from the null hypothesis in 3-dimensional brain space.^[37,38]^ The images will be subjected to rigorous quality control assessments. Artefact-free, good quality data will be subjected to standard pre-processing and first-level design specification analysis. This will be followed by second-level random effect analyses to examine for differences in BOLD response among study groups, treatment effects (i.e., baseline versus follow-up comparison) as well as the correlation between the BOLD response and various other study parameters (clinical symptoms scores, and other neurobiological parameters). The specific contrast of interest will be BOLD signal differences during the performance of emotion processing tasks between the 2 groups at baseline as well as analysis for interaction effects (pre versus post). The voxel-wise analysis will produce a statistical parametric map in the stereotactic space of the Montreal Neurological Institute.^[39]^ Significance corrections for multiple comparisons will be performed using a family-wise error correction (*P* < .05). The coordinates of significant areas of activation will be transformed from MNI space into the stereotactic space of Talairach and Tournoux. Resting-state functional images will be processed using the CONN functional connectivity toolbox^[40]^ and DPABI toolbox^[41]^ for analyzing the changes in functional connectivity, regional homogeneity, amplitude of low-frequency fluctuation (ALFF), and fractional ALFF. DTI will be processed using the tract-based spatial statistics pipeline^[42]^ to examine for changes in fractional anisotropy and diffusivity measures in white matter tracts.

Table 1 gives the schedule of assessments in the study.

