**Methods::**

This is a randomized-controlled clinical study including patients from an urban tertiary hospital and a semi-urban community center, with a between-group, repeated-measures, longitudinal design. This study will recruit 160 patients with DSM 5 diagnosis of schizophrenia who are on stable medication for a minimum of 6 weeks; they will be randomly assigned into 2 arms viz., yoga therapy (YT), and treatment-as-usual (TAU) with 80 patients in each arm. Participants will undergo Clinical, Laboratory, and Radiological assessments at baseline and at intervals of 1 month, 3 months, and 6 months from the baseline. It is hypothesized that yoga will improve psychopathology and emotion processing, increase serum brain derived neurotrophic factor (BDNF) and plasma oxytocin levels and effect changes in cerebral activation in areas of the brain associated with schizophrenia.

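### The BOLD plan calls the before/after change the treatment effect and lists a baseline arm comparison as a contrast of interest; the valid group-by-time interaction is present but has neither the label nor priority

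*Protocol article*

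**What the plan says.** The BOLD response is a primary outcome (section 2.4) and the subject of a primary hypothesis (section 1.3.1, item 3). Three statements fix how it will be analysed.

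- **Section 2.4, primary outcome measures.** The BOLD item has two parts: differences among the study groups and, separately, "treatment effects (i.e., baseline vs follow-up comparison").
- **fMRI processing and analysis paragraph, at the end of section 2.5.1.4.** The second-level analyses are "to examine for differences in BOLD response among study groups", then "treatment effects (i.e., baseline versus follow-up comparison"), then correlations with other measures. No time point is given for the among-groups comparison.
- **Same paragraph, next sentence.** "The specific contrast of interest will be BOLD signal differences during the performance of emotion processing tasks between the 2 groups at baseline", continuing directly with "as well as analysis for interaction effects (pre versus post").

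The abstract describes a randomised trial "with a between-group, repeated-measures, longitudinal design". Section 2.3 gives 1:1 allocation, and section 2.2.1 gives an imaging subset of 50 per arm, scanned before and after.

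**The concern.** The wording in both places equates the treatment effect with a comparison over time. In one arm, such a comparison picks up everything that changes between scans: yoga, but also habituation to the faces, familiarity with the scanner and task, regression to the mean, and continuing medication. The treatment-as-usual arm is there to remove these, and a before/after contrast does not use it.

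The baseline comparison of arms precedes the intervention. With random allocation its expected value is zero whether or not yoga works, so it cannot inform the efficacy question.

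At stake is a primary claim. Hypothesis 3 speaks of changes in cerebral activation and names no comparison. Under the plan's own definition, a significant before/after change in the yoga arm could be reported as a treatment effect even if the control arm changed just as much.

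**Working it through.** The plan gives no figure for this contrast, so there is none to reproduce. The check is what each named contrast estimates, followed by an illustration of size.

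**1. What each contrast estimates.** Let Δ be the mean change over time common to both arms and τ the effect of yoga on change.

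| Contrast in the plan | Expected value | Estimates yoga effect? |
|---|---|---|
| Baseline versus follow-up, yoga arm | Δ + τ | Only if Δ = 0 |
| Baseline versus follow-up, arms pooled 1:1 | Δ + τ/2 | No |
| Yoga minus control at baseline | 0 | No, whatever τ is |
| Group-by-time interaction | (Δ + τ) − Δ = τ | Yes |

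**2. Inputs for the illustration.** n = 50 per arm (section 2.2.1). *Assumed*: one scalar BOLD summary, two-sided 0.05, τ = 0, and Δ equal to 0.2, 0.3 or 0.5 SD of the change score. The protocol gives no drift figure, so these are a range.

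**3. Before/after test in the yoga arm.** One-sample t on change, 49 degrees of freedom, critical value about 2.01, noncentrality Δ√n with √50 = 7.071:

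- Δ = 0.2: noncentrality 1.414, rejection probability 0.283
- Δ = 0.3: noncentrality 2.121, rejection probability 0.548
- Δ = 0.5: noncentrality 3.536, rejection probability 0.934

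All of these rejections would be wrongly credited to yoga, since τ = 0.

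**4. Simulation check.** 4,000 runs per setting, 50 per arm, pre-post correlation 0.5 (assumed). The SD of change is then √(2(1 − 0.5)) = 1, so drift is on the same scale as in step 3.

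| Setting | Baseline contrast | Yoga before/after | Interaction |
|---|---|---|---|
| Δ = 0.3, τ = 0 | 5.1% | 54.9% | 4.8% |
| Δ = 0.5, τ = 0 | 5.3% | 93.8% | 4.7% |
| Δ = 0, τ = 0.5 | 5.1% | 93.1% | 69.0% |

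The before/after test cannot tell row 2 (drift, no effect) from row 3 (effect, no drift). The interaction can. The baseline contrast stays near 5% throughout, including when yoga works.

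**5. Multiplicity correction.** The plan applies family-wise error correction at P < .05 across voxels. This controls false positives over many locations when nothing has changed. A shared time effect is a real change in signal, so the correction does not remove it.

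**The case against.** The strongest reply is that the valid analysis is already planned. The sentence on the contrast of interest includes "as well as analysis for interaction effects (pre versus post"), which after the reference to the two groups is most naturally the group-by-time interaction. The words joining the two items do not rank them, and differences among study groups are listed before treatment effects in both places. This stands. A reader who stops at the word baseline might infer that the imaging plan has no randomised contrast; the rest of the sentence refutes that.

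Three other stronger readings also lack support:

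- **That the clinical and laboratory outcomes share the fault.** In section 2.4 the baseline-versus-follow-up definition belongs to the BOLD item, and a mixed model is named for the analysis.
- **That the baseline test uses up error rate.** The protocol sets no division of alpha between these contrasts, and a chance difference at baseline cannot itself be reported as a yoga effect.
- **That 28%, 55% and 93% are error rates of the planned analysis.** They describe one scalar under assumed drift. The plan specifies voxel-wise inference with family-wise correction.

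It is also fair that the scanned and analysed subset may be altered by dropout or scan quality after randomisation, so describing its baseline comparability has some use. That supports a descriptive table, not a contrast of interest. Finally, ranking contrasts is often left to an analysis plan. Here, however, the article itself states the definition and the contrast, so these are choices made rather than details omitted.

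**Conclusion.** The point holds, limited to the BOLD outcome. The plan contains the right contrast but attaches the name treatment effect to a different one that does not isolate yoga. It also puts an uninformative baseline comparison beside the interaction in the contrast of interest. Followed as written, it lets a primary claim about brain activation rest on a change that the control arm may share.

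The algebra needs only random allocation. The size depends on the assumed drift: a false before/after finding in about 28% to 93% of trials for shared drift of 0.2 to 0.5 SD of change, against about 5% for the interaction. With no shared drift, the before/after test would also reject at about 5% when yoga has no effect.

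**What to change.** In section 2.4 and in the fMRI analysis paragraph:

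1. Define the BOLD treatment effect as either the group-by-time interaction or the between-arm difference at follow-up adjusted for baseline, and make it the primary BOLD contrast. Name one. Under randomisation they have the same target but are different estimators. At a pre-post correlation of 0.5 (assumed), their variances stand in the ratio 2(1 − 0.5) = 1.00 for the change-score interaction to 1 − 0.5² = 0.75 for baseline adjustment, and they can disagree if baselines differ.
2. Remove the between-group difference at baseline from the contrast of interest. Keep any baseline comparison of the imaging subset descriptive.
3. Report before/after change within each arm descriptively, and do not call it a treatment effect.

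The cost is a change of wording in two places. No new data, scans or patients are needed.

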#### Primary hypotheses

1.3.1

In patients with schizophrenia, add-on yoga-based intervention will lead to:

1.Improvement in psychopathology and emotion processing in patients with schizophrenia.2.Increase in serum BDNF and plasma oxytocin levels in patients with schizophrenia.3.Changes in cerebral activation in areas of the brain associated with symptoms of schizophrenia (limbic area and prefrontal cortex).

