#### Sample size estimation

2.2.1

For evaluating the primary objectives, the optimal sample size was estimated using the principles and methods^[31]^ for the assessment of primary parameters (SAPS, SANS, and BPRS scores, serum BDNF, Oxytocin, TRENDS fMRI). Based on approximation and estimation from the previous data on the clinical effects of add-on yoga therapy on these parameters in schizophrenia patients^[7,16,18]^ supporting a medium effect size for yoga-based intervention, it was estimated that, for an allocation ratio of 1, a sample size of at least 67 schizophrenia patients in each arm for the pre- versus post- comparisons of patients will be required to detect a two-tailed significant difference of *α* = 0.01 with an estimated 90% power. The study plans to recruit 80 patients in each arm (a total of 160 patients) to account for potential drop-outs.

The subset sample size of 50 in each arm for imaging studies (in each group—pre as well post brain scans) is sufficient to perform random effect analysis for fMRI BOLD changes with multiple comparison correction using random field theory based family-wise error correction to control for multiple comparison (http://www.fil.ion.ucl.ac.uk/spm/).

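### The primary BOLD endpoint is not tied to the limbic and prefrontal regions named in primary hypothesis 3, and its family-wise correction has no stated search volume

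*Protocol article*

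**What the plan says.** Four places in the protocol article bear on this.

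- **Section 1.3.1, primary hypothesis 3** is regional: "Changes in cerebral activation in areas of the brain associated with symptoms of schizophrenia (limbic area and prefrontal cortex". It gives no direction of change.
- **Section 2.4, primary outcome measures**, gives the BOLD endpoint as "differences in BOLD response among study groups, and treatment effects (i.e., baseline vs follow-up comparison". No region, mask or regional summary is named.
- **The fMRI analysis paragraph after section 2.5.1.4** describes inference with SPM "regarding deviations from the null hypothesis in 3-dimensional brain space". The contrast of interest is "BOLD signal differences during the performance of emotion processing tasks between the 2 groups at baseline as well as analysis for interaction effects". It continues: "The voxel-wise analysis will produce a statistical parametric map in the stereotactic space of the Montreal Neurological Institute", and "Significance corrections for multiple comparisons will be performed using a family-wise error correction" at P < .05. Coordinates are then reported for the areas that reach significance, wherever they lie.
- **Section 2.2.1** provides "The subset sample size of 50 in each arm for imaging studies" and calls it sufficient for a random-effects analysis with random-field family-wise correction. It gives no effect size, power or search volume.

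No region of interest, anatomical mask or small-volume correction appears in the article.

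**The concern.** The hypothesis says where the effect should be, and the endpoint that is meant to test it does not. Two things follow if the analysis is run unmasked, which is the default reading of a voxel-wise map with no mask named.

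1. **Interpretation.** Family-wise correction limits false positives over the volume searched. It does not connect success to the predicted areas. The tasks present face images, so a significant cluster in visual cortex, for example, is plausible. Section 2.4 contains nothing that stops it being counted as a positive primary BOLD result, although hypothesis 3 does not predict it.
2. **Sensitivity.** A real limbic or prefrontal effect has to pass a threshold set for a much larger volume than the hypothesis needs, in a subset of 50 per arm.

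**Working it through.** **The plan's own figure.** The 50 per arm cannot be reproduced, because no effect size, power or search volume is given for it.

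**Inputs from the documents.** 50 per arm; random-field family-wise correction at 0.05; 3.0 mm isotropic voxels (27 mm³).

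**Assumptions, not in the documents.** Two-sample comparison of change, ν = 50 + 50 − 2 = 98 df; 0.025 per tail; whole brain 1.4 L; combined limbic and prefrontal mask 0.10-0.25 L; smoothness F = 8, 10 or 12 mm FWHM; search volume treated as a sphere of radius r; standardised arm difference in change d = 0.5 or 0.8. The only effect-size statement in section 2.2.1 is that it is medium, with no number; d = 0.5 is one reading of that.

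**Threshold.** Solve for u in R0·ρ0 + R1·ρ1 + R2·ρ2 + R3·ρ3 = 0.025, where

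- R0 = 1, R1 = 4r/F, R2 = 2πr²/F², R3 = (4/3)πr³/F³
- A = (1 + u²/ν)^(−(ν−1)/2)
- ρ0 = P(T > u)
- ρ1 = √(4 ln 2)/(2π) · A
- ρ2 = 4 ln 2/(2π)^1.5 · Γ((ν+1)/2)/[√(ν/2)·Γ(ν/2)] · u · A
- ρ3 = (4 ln 2)^1.5/(2π)² · [((ν−1)/ν)u² − 1] · A

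Example, whole brain at F = 10: r = 69.4 mm, so R = 1, 27.8, 302.6, 1400. At u = 5.28 the four terms are about 0.0000 + 0.00004 + 0.0015 + 0.0234 = 0.025.

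**Single-voxel power.** P(T > u) for a noncentral t with 98 df and noncentrality d·√(50/2) = 5d, that is 4.0 at d = 0.8 and 2.5 at d = 0.5.

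| FWHM | Search volume | Threshold t | Power, d = 0.8 | Power, d = 0.5 |
|---|---|---|---|---|
| 8 mm | 1.4 L | 5.45 | 9.0% | 0.3% |
| 8 mm | 0.25 L | 4.99 | 17.8% | 1.0% |
| 8 mm | 0.10 L | 4.74 | 24.5% | 1.7% |
| 10 mm | 1.4 L | 5.28 | 11.8% | 0.5% |
| 10 mm | 0.25 L | 4.81 | 22.6% | 1.5% |
| 10 mm | 0.10 L | 4.55 | 30.4% | 2.6% |
| 12 mm | 1.4 L | 5.13 | 14.7% | 0.7% |
| 12 mm | 0.25 L | 4.66 | 27.1% | 2.1% |
| 12 mm | 0.10 L | 4.39 | 35.8% | 3.6% |

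**Sensitivity to the assumptions.** A second set uses a one-sided contrast at 0.05, a 1.5 L brain, a 0.15-0.30 L mask, and the smaller of the random-field and Bonferroni thresholds. It gives t = 4.96-5.08 unmasked and 4.29-4.69 masked. Power at d = 0.8 is 16-19% against 26-39%; at d = 0.5 it is about 1% against 2-4%. The direction and rough size do not change.

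Single-voxel power understates the chance of detecting an effect that spans many voxels. The figures are best read as a comparison of the two search volumes, not as the power of the imaging study.

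**The case against.** The strongest reply is that this is a condensed article. Masks and search volumes are details that a full protocol or analysis plan may hold, and voxel-wise family-wise correction is equally compatible with correction inside a mask. That is fair as far as it goes. A reader might infer that the endpoint is declared to be any voxel in the brain, but the article does not say so: the phrase about brain space is a general description of SPM, and the search volume is unstated. What remains is not only missing detail. The article sets out the software, inference theory, contrast, coordinate space and correction, and the regions of section 1.3.1 drop out where the endpoint is defined.

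A reader might also conclude that the analysis does not test hypothesis 3 at all. That is too strong. The map contains limbic and prefrontal voxels, and significant ones there would support the hypothesis with valid, if conservative, error control. Nor does any passage state that a cluster elsewhere confirms hypothesis 3; reported coordinates would let a reader see where it lies. The weakness is that nothing ties success on the primary outcome to the predicted areas.

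Primary objective 2 names fMRI without a region, and the abstract speaks only of areas associated with schizophrenia, so a wider search serves those statements. This supports keeping the whole-brain map, but not leaving the regional hypothesis without a regional endpoint.

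Finally, the sensitivity argument depends on d = 0.8, which the documents do not give. At d = 0.5 masking barely helps. A larger gain can be shown with a bilateral amygdala mask (4 mL, 10 mm FWHM: t = 3.61, 65% at d = 0.8), but neither hypothesis 3 nor the fix below is confined to the amygdala, so that figure should not be used here.

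**Conclusion.** The point holds in a limited form. Hypothesis 3 is regional, while its primary BOLD endpoint and analysis carry no region and no stated search volume. If run unmasked, the endpoint could be called positive on a finding that the hypothesis does not predict, and some available sensitivity is lost. The loss is modest: 9-15% against 18-36% single-voxel power at d = 0.8, and under 4% with or without the mask at d = 0.5. These figures rest on assumed volumes, smoothness, effect size and 0.025 per tail. The main reason to act is the link between hypothesis and endpoint; power is secondary. The error control is not invalid.

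**What to change.** Define the primary BOLD endpoint as the group-by-time interaction on the emotion-processing task contrast, within limbic and prefrontal atlas masks fixed before unblinding and family-wise corrected within those masks (small-volume correction). State the masks and the search volume.

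Say which task is primary. The analysis paragraph refers to emotion-processing tasks in the plural, and section 2.2.1 lists TRENDS fMRI among the primary parameters, so the documents do not support choosing E-MALT alone by default. If both E-MALT and TRENDS stay primary, share the error rate across them.

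Keep the whole-brain map as exploratory, and state that clusters outside the masks do not count as support for hypothesis 3.

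Cost: analysis-plan wording and two atlas masks, with no new scans or patients. The downside is that effects outside the masks become exploratory.
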